# Building Emotional Awareness and Mental Health (BEAM): study protocol for a hybrid implementation-effectiveness trial of the BEAM app-based program for parents with clinical mental health problems

**DOI:** 10.1186/s12888-025-06964-4

**Published:** 2025-06-02

**Keywords:** Parenting, Mental health, Depression, Anxiety, Psychoeducation, App-based intervention

## Abstract

**Background:**

Children are highly sensitive to adversity during their first five years of life, with exposure to chronic parental mental illness (MI) consistently linked to socio-emotional impairments and mental health problems in children. Children born during the COVID-19 pandemic were exposed to unprecedented levels of parental distress, with parental MI reported at three times the pre-pandemic rates. This situation underscored a pressing need for scalable solutions to foster positive mental health and developmental outcomes for a generation of children. In response, we developed the Building Emotional Awareness and Mental Health (BEAM) program, an innovative mobile health (mHealth) solution for parents of young children. Clinical trials to date evaluating BEAM have shown promising results, demonstrating reductions in parent depression, suicidality, anxiety, and harsh parenting practices. This trial involves an effectiveness-implementation hybrid design with co-primary aims of (1) determining BEAM’s effectiveness in improving parent mental health, and (2) evaluating the implementation of BEAM in the community through metrics such as feasibility, acceptability, and uptake. This trial’s secondary aim is to measure BEAM’s effectiveness in improving short-term child mental health and developmental outcomes using primary data and long-term psychosocial family outcomes using administrative data. A final exploratory aim of this trial will measure the cost-utility of delivering BEAM relative to extant health programming.

**Methods:**

A single arm trial with repeated measures will be used to evaluate the effectiveness of implementing the BEAM intervention in the community with a sample of 400 parent participants with a child aged 24–71 months. Participants must self-report moderate to severe symptoms of depression, anxiety, parenting stress, and/or anger at time of enrolment (T0) and live in the province of Manitoba, Canada. Individuals will be recruited through four streams including the (1) Manitoba Crisis Response Services, (2) primary care offices (paediatricians and/or general practitioners), (3) Manitoba family community organizations and child care centres, and (4) social media. Study participants will complete 12 weeks of psychoeducation modules, with access to an online social support forum and check ins with a peer coach. Assessments of parent and child mental health symptoms will occur at pre-test before BEAM begins (T1), immediately after the last week of the BEAM intervention (post-test, T2), 6-month follow-up (T3), and 12-month follow-up (T4).

**Discussion:**

The BEAM program offers a promising solution to address elevated parental mental health symptoms, parenting stress, and related child functioning concerns. The present implementation trial aims to extend the groundwork established by an open pilot trial and RCT of the BEAM program, in a next step of testing BEAM’s readiness for nationwide scaling.

**Trial registration:**

ClinicalTrials.gov NCT06455397. Registered on June 11, 2024.

## Administrative information

Note: the numbers in curly brackets in this protocol refer to SPIRIT checklist item numbers. The order of the items has been modified to group similar items (see http://www.equator-network.org/reporting-guidelines/spirit-2013-statement-defining-standard-protocol-items-for-clinical-trials/).

## Introduction

### Background and rationale {6a}

The initial five years of a child’s life mark a critical developmental phase and a period of high sensitivity to environmental stressors, including the impact of parental mental illness (MI) and parenting stress. Research has consistently linked parental MI with a broad range of child-related issues, including irritability, sleep disturbances, and socio-emotional developmental impairments [1–4]. These adverse outcomes are often attributed to environmental factors, including parental modeling of maladaptive emotion coping strategies such as avoidance, aggression, and harsh parenting practices characterized by reactive discipline and conflictual interactions [5–7]. Notably, when parental MI is accompanied by additional stressors such as domestic conflict or financial strains, the long-term risks for children are exacerbated [8]. Further, the chronicity of parental MI has critical implications for children. When stressors and parental MI are persistent, the risk of adverse developmental outcomes for children increases, putting children at heightened risk for stress and development of their own psychopathology [9, 10]. This highlights the critical need for interventions that address parental MI and the broader spectrum of parenting stress and its multifaceted impacts on children.

Despite the need for parents to improve their stress and mental health symptoms, the majority of families do not have access to evidence-based treatments [2, 3, 11]. Previous research has documented many barriers preventing parents from accessing care. These barriers include service backlogs, long waitlists, high costs of individual therapy, lack of information of where to access interventions, perceived need for care, stigma, and overwhelming childcare demands [2, 3, 11–15]. Additionally, although evidence-based treatments exist, most interventions do not comprehensively address the mental health of both parents and children. This gap in services is significant, given meta-analytic evidence indicating that dual-generation programs, which simultaneously target parent MI and child well-being, yield impacts that are 50% larger in promoting positive child outcomes compared to programs focused solely on addressing parental MI [10]. There is a clear need to provide accessible and scalable solutions that promote positive mental health and developmental outcomes in at-risk children. mHealth (i.e., the use of mobile devices, such as cellphones and tablets, for healthcare delivery) interventions offer a potential avenue for addressing family needs and barriers to care that are an accessible and low-cost option, and research shows great promise for treating adult depression using these methods [16]. Additional emerging research highlights the efficacy of app-based programs in improving parental MI and parent–child interactions [17, 18]. However, very limited existing app-based or mHealth programs address both parental mental health and parenting skills, which indirectly targets child well-being.

### Building emotional awareness and mental health program

In response to this need, we conducted qualitative research (i.e., focus groups and individual interviews with parents with lived experience) and consulted our parent advisory board with the aim of co-developing a program that simultaneously addressed parental MI and parenting. We found that parents wanted accessible, online services grounded in expert research [19–21]. Alongside patient-partners and community providers, we then developed the BEAM (Building Emotional Awareness and Mental Health) app-based program. The BEAM program is aligned with best practices in mHealth programs including patient-driven priorities, rapid-cycle iterations to facilitate continual improvements, and a commitment to evidence-based care [22–24]. Key elements of the original BEAM program include: (1) expert-led educational videos using transdiagnostic therapy [25, 26] and emotion-focused parenting strategies [20]; (2) brief group sessions to consolidate therapeutic content and build social support [27, 28]; (3) a community forum to enhance social connection; and (4) symptom monitoring to track progress [29]. In case of a mental health or parenting-related crisis, clinical coaches also consult with the registered psychologists on the research team via phone. BEAM builds on evidence from our knowledge synthesis work that mHealth therapeutics can address parent MI and appeals to parents [22, 23, 30].

The BEAM intervention has consistently demonstrated promising outcomes across various trials to date. We first conducted an open pilot and pilot RCT which demonstrated BEAM’s efficacy in reducing MI symptoms such as depression, anxiety, anger, sleep issues, and substance use [31, 32]. In our latest phase II RCT with mothers of toddlers, the BEAM program outperformed a services-as-usual (SAU) control condition [33]. Significant improvements in parental MI symptoms including anxiety, anger, and alcohol use were observed. Additionally, BEAM was effective in reducing harsh parenting practices and negative parent–child interactions, with substantial improvements observed for families living in poverty. This trial also showed noteworthy participant engagement with retention rates (84%), comparable to in-person therapy sessions [34]. Qualitative feedback from the initial trials emphasized the positive impact of the BEAM program on mental health and parenting, leading to enhanced quality of life and improved family relationships. Participants also highlighted the value of the social support gained through the online community [31, 32].

### The present study

To further address family mental health needs, we aim to test the readiness of the BEAM program for scalability. The current study involves a hybrid effectiveness-implementation trial design to build on our previous work. Specifically, effectiveness and implementation are co-primary outcomes. We will evaluate effectiveness by examining short-term change in parent mental health symptoms using primary data and longer-term change in family health and psychosocial outcomes with linked administrative data. We will evaluate implementation using objective and subjective metrics of feasibility, acceptability, and uptake at post-intervention. Our hybrid design follows the “type 2” model [35], in which effectiveness and implementation are co-primary aims and can be tracked simultaneously as the trial progresses. This approach is consistent with our rapid-cycle program development in which we have sought to test and adapt BEAM in response to patient and provider feedback through each iteration.

Through this implementation trial we aim to maximize BEAM’s accessibility, equitability, and effectiveness for future nation-wide implementation. For the current trial, we conducted an app rebuild to create BEAM Version 2.0 based on participant and parent advisory board feedback. BEAM 2.0 updates include improvements to psychoeducational video content (e.g., high-quality video production, animations, closed captioning), the mobile application user experience (e.g,. push notifications, direct messaging, integrated video player that adjusts video quality based on bandwidth, easy-to-navigate platform), and functionality across mobile device operating systems (iOS, Android). The weekly psychoeducational videos, short symptom monitoring surveys, and social support community forum are housed seamlessly within the BEAM app. Other aspects of the program include individual check ins with trained peer coaches, group drop-in sessions that are facilitated by peer coaches where experts may be invited to discuss topics of interest (e.g., child psychologist, speech pathologist, paediatrician), and a connection to a Systems Navigator, whose role will be to support participants in accessing resources in their community. See Fig. 1 for an overview of all BEAM program components.

**Fig. 1 Fig1:**
[figure not shown]
BEAM Version 2.0. Program Components. Note. Expert-led videos provide weekly psychoeducational mental health and parenting content within the BEAM app. Guided content review and individualized support is led by trained peer coaches. Symptom monitoring allows participants to complete brief weekly symptom tracking surveys in app. The community forum facilitates communication and connection with other program participants. The Systems Navigator can support participants in accessing community resources (e.g., childcare programs, legal aid, housing). Consistent with a stepped care approach, responsive crisis consultation will be provided by the BEAM Clinical Team

### Objectives {7}

The objective of the present intervention study is to conduct an effectiveness-implementation hybrid trial with co-primary aims of (1) determining BEAM’s effectiveness in improving parent mental health challenges (2) evaluating the implementation of BEAM in community agencies through metrics of feasibility, acceptability, and uptake. With respect to co-primary aim (1), we hypothesize that enrolled parents will evidence improvements in self-reported mental health (primary outcome) across four timepoints. Additionally, we hypothesize that enrolled parents will display reductions in parenting stress and harsh parenting behaviours, and report improvements in child mental health and developmental outcomes (secondary outcomes) across four timepoints. With respect to co-primary aim (2), we hypothesize that BEAM will meet quantitative and qualitative benchmarks of feasibility, acceptability, and program uptake that will motivate implementation of BEAM at greater scale.

We additionally aim to evaluate BEAM’s effectiveness in improving long-term health and psychosocial child and family outcomes relative to two population-based control cohorts. Using a natural experiment, we will construct ‘population-average’ and ‘risk-matched’ control cohorts from administrative data in the province of Manitoba, Canada. The ‘population-average’ cohort will consist of parents who match the basic demographics of BEAM participants and their children (e.g., age, number of children, etc.), while the ‘risk-matched’ cohort will consist of parents who match the basic demographics as well as the physical health, mental health, developmental, and service utilization characteristics of BEAM participants and their children (e.g., vaccination records, mental illness diagnoses, school literacy/numeracy benchmarks, hospitalization records). Administrative data will be drawn from childbirth (as early as January 2018) to as much as five years post-intervention (with an end date of June 2030). We hypothesize that participants who receive BEAM will evidence improvements in administrative measures of physical health, mental health, and developmental outcomes relative to the population-average and risk-matched cohorts.

The current study also includes the examination of baseline moderators (e.g., discrimination experiences, adverse child experiences) and exploratory variables (e.g., positive parenting, social support) which may be examined as exploratory outcomes, moderators, or mechanisms of change. Additionally, exploratory health economic outcomes pertaining to cost-utility will be examined (e.g., program delivery cost per quality-adjusted life-year [QALY]). With the goal of maximizing population health, a cost-utility analysis will compare BEAM’s delivery cost per QALY to that of extant programming [36, 37]. Other exploratory aims may be developed based on identified need and interest from partner community organizations, knowledge users, and collaborators.

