### Eligibility criteria {10}

#### Inclusion and exclusion criteria

Eligibility includes: identifying as a parent with a child aged 24–71 months, English speaking, at least the age of 18 years, and residing in Manitoba, Canada. Parents must also self-report: moderate-to-severe symptoms of depression (≥ 10) on the Patient Health Questionnaire (PHQ-9) [42], and/or anxiety (≥ 10) on the General Anxiety Disorder (GAD-7) scale [43], and/or clinical levels of parenting stress (total score ≥ 110, parental distress subscale ≥ 38, parent–child dysfunctional interactions subscale ≥ 31, difficult child subscale ≥ 38) on the Parenting Stress Index – 4 th Edition – Short Form (PSI-4-SF)) [44], and/or clinical levels of anger (≥ 16) using the Patient-Reported Outcomes Measurement Information System (PROMIS-Anger) [45] at time of enrolment (T0). Parents with no self-reported symptom scale elevations but who are otherwise eligible will meet with a member of the BEAM team to determine eligibility. This eligibility decision will be based on clinical judgement, ensuring that those with need can participate. Eligible parents will be asked if they are available and willing to join the 12-week program and whether they can participate in regular individual check ins (15 to 60 min) via videoconference, phone, or direct messaging with a peer coach.

In terms of exclusion criteria, given that the BEAM program is not designed to support the needs of individuals at high risk for suicide and/or self-harm, parents who report self-harm that required medical attention within the past six months, a suicide attempt within the past year, or active thoughts of suicide with a plan will be ineligible without additional supports in place. These parents must be engaged in or on a waitlist for individual therapy with a psychiatrist, psychologist, social worker, or regulated mental health professional for the duration of their BEAM involvement. Parents at risk for suicide or self-harm who are not actively engaged in individual therapy will meet with a member of the BEAM team to be connected with or placed on a waitlist for these services before engaging in the BEAM program. Individuals who have participated in prior versions of the BEAM program will be excluded.

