### Assignment of interventions: allocation

Not applicable, there will be no assignment to different interventions.

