Analysis of administrative-linked outcomes will enable comparisons between BEAM families and those families in ‘population-average’ and ‘risk-matched’ control cohorts drawn from MCHP’s provincial administrative database. While the ‘population-average’ control cohort will be comprised of parents who match the basic demographics of BEAM participants and their children (e.g., age, number of children), the ‘risk-matched’ control cohort will consist of parents of young children who match the demographics, physical health, mental health, child developmental, and service utilization characteristics of BEAM participants and their children. This will be accomplished in consultation with MCHP by matching Manitoban families in the administrative database to BEAM families on these risk factors. These matching criteria will be developed using MCHP’s high-dimensional propensity scores matching algorithm (hdPSs) which, across multiple algorithmic iterations, identifies risk factors that are correlated with the features of the participants who have enrolled in the BEAM program [71]. This data-driven propensity score development strategy is commonly used and will allow our team to match BEAM participant risk to non-BEAM participants in the community. Comparing trajectories in health and social outcomes between BEAM participants, ‘risk-matched’ controls, and ‘population-average’ controls will generate knowledge about the extent to which children experience stable, cumulative, or “sleeper” (i.e., not observable until after developmental time periods) benefits over time. If we find children experience diminishing effects such that program benefits are only present in the first year, this may indicate that further intervention is required to sustain program achievements. All administrative-linked analyses will be conducted by MCHP statisticians.

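### The administrative comparison is called a natural experiment, but parents self-select on current symptoms that no listed record source holds for controls, so a risk-matched difference is an association and not shown effectiveness

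*Protocol article*

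**What the plan says.** Objectives {7} states the aim to "evaluate BEAM’s effectiveness in improving long-term health and psychosocial child and family outcomes relative to two population-based control cohorts". It names the design in introducing the control cohorts, "Using a natural experiment, we will construct", and hypothesises that "participants who receive BEAM will evidence improvements in administrative measures of physical health, mental health, and developmental outcomes" relative to both the population-average and the risk-matched cohort.

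The risk-matched cohort is built by high-dimensional propensity scores on variables in the provincial database. Statistical methods {20a} says that this "will allow our team to match BEAM participant risk to non-BEAM participants in the community". The same section would take a difference that fades after the first year as diminishing program benefit and a possible sign that more intervention is needed.

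On how families come to be exposed, the allocation section says "Not applicable, there will be no assignment to different interventions". Recruitment runs through crisis services, primary care, community organizations and social media. Under Inclusion and exclusion criteria, "Parents must also self-report: moderate-to-severe symptoms of depression", or elevated anxiety, parenting stress or anger, at T0. Parents with no elevated scale can still enter after a meeting with the team: "This eligibility decision will be based on clinical judgement, ensuring that those with need can participate". Eligible parents must also be available and willing.

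Administrative measures lists diagnoses, visits, admissions, prescriptions, a family screening form, education data and similar sources. It links self-report scores to the records of BEAM participants only.

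**The concern.** In a natural experiment, something outside the control of the people studied determines who is exposed, such as a policy date, a boundary or a capacity limit. The protocol describes nothing of that kind. The BEAM group is defined by parents seeking or accepting help at a time of elevated symptoms, and the controls are families who did not enrol.

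The self-report arm has no concurrent control, so the administrative analysis is the trial's only between-group comparison and carries the long-term effectiveness claim. If current symptoms and motivation remain unbalanced after matching on recorded history, the BEAM and matched families can differ afterwards even if the program does nothing. Under the present wording, that difference would be read as lasting benefit, lack of benefit or fading benefit.

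**Working it through.** **No plan figure to reproduce.** The protocol gives no sample size, effect size or power for the administrative comparison. N = 400 was set for the self-report mixed model, and this point does not depend on it.

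**What drives entry, and whether controls have it**

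| Driver of enrolment | BEAM families | Controls |
|---|---|---|
| T0 depression, anxiety, parenting stress and anger scores | recorded and linkable | no listed source |
| Clinical judgement of need | made by the team | none |
| Willingness to join and to meet a coach | required | not recorded |
| Past diagnoses, prescriptions, service use, screening form | in records | in records |

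Matching can act only on the last row. Those variables are partial proxies for the first three.

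**Illustration 1: how large a false difference could be.** All inputs are assumptions. Recorded history H ~ N(0,1). Current symptoms S = 0.5H + noise, scaled to unit variance and unrecorded. Enrolment logit = −6 + 0.5H + bS. One-year event logit = −2 + 0.4H + gS. BEAM has no effect. Controls are matched exactly on H. With p the enrolment probability and q the event probability:

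- BEAM risk = E[pq] / E[p]
- Matched-control risk = E{ E[p|H] × E[(1−p)q|H] / E[1−p|H] } / E[p]

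Numerical integration gives:

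| b | g | BEAM risk | Matched-control risk | Risk ratio |
|---|---|---|---|---|
| 0.5 | 0.3 | 0.202 | 0.185 | 1.09 |
| 0.5 | 0.7 | 0.270 | 0.228 | 1.18 |
| 1.0 | 0.3 | 0.239 | 0.203 | 1.18 |
| 1.0 | 0.7 | 0.345 | 0.253 | 1.36 |
| 1.5 | 0.3 | 0.268 | 0.214 | 1.25 |
| 1.5 | 0.7 | 0.407 | 0.268 | 1.52 |

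Every ratio is above 1, which is against BEAM.

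**Illustration 2: what a placebo date can detect.** Optional linkage with more than 80% opting in gives about 0.80 × 400 = 320 linked parents. With five controls each (assumed), the difference detectable with 80% power at two-sided 0.05 is (1.960 + 0.842) × √(1/320 + 1/1600) = 0.17 SD. A second simulation, again with no BEAM effect, assumed records that correlate 0.5 with symptoms, enrolment driven by current symptoms, and adjustment on two earlier record years. The placebo analysis moves the outcome window one year back and adjusts only on records before it.

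| Stable share of symptom variance | False BEAM difference (SD) | Placebo difference (SD) | Power of placebo check | False minus placebo (SD) |
|---|---|---|---|---|
| 0 | 0.39 | 0.02 | about 6% | 0.37 |
| 0.25 | 0.48 | 0.20 | 91% | 0.28 |
| 0.50 | 0.52 | 0.36 | >99% | 0.16 |
| 0.75 | 0.52 | 0.48 | >99% | 0.04 |

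The check exposes lasting selection. It shows almost nothing when the excess is a short peak at enrolment, although the false difference is then still 0.39 SD. Subtracting the placebo value leaves 0.04 to 0.37 SD of false effect.

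**Look-back.** Children are 24 to 71 months old at entry and records run from birth. A placebo date 12 months earlier leaves 24 − 12 = 12 months of prior records for the youngest and 71 − 12 = 59 for the oldest.

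**The case against.** The strongest reply is that the design is in plain view. The protocol openly describes matched cohorts of non-participants, the aim is secondary, some of the wording is hedged, and the label is a matter of terms. Balance diagnostics and falsification analyses are usually left to an analysis plan, which is not shown here. The records are also rich, with diagnoses, prescriptions, emergency visits, admissions, a mental health information system and a screening form that covers mental health, and the plan already intends to look at trajectories from childbirth.

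Much of this stands. The absence of a described check is not by itself a finding, and the records should reduce confounding by more than the one-variable history in Illustration 1 allows. What does not fall away is what the document itself states: a design label whose defining property is absent, an effectiveness aim resting on it, and an assurance that the score will match participants' risk.

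A reader might go further and infer that a placebo-date run would settle whether the risk-matched difference is causal, or could be subtracted to correct it. Illustration 2 contradicts both, because a peak confined to enrolment is the case the check misses. A reader might also infer that bias in both directions has been shown. It has not: every quantified scenario runs against BEAM, and the favourable direction is an argument only.

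**Conclusion.** The point holds as a matter of design description and of what may be concluded. The comparison is a matched observational cohort of volunteers, and a risk-matched difference does not by itself show effectiveness. With a null program, residual selection on unrecorded current symptoms gave risk ratios of about 1.1 to 1.5, or 0.39 to 0.52 SD against a detectable difference of about 0.17 SD. These sizes rest on assumed coefficients and correlations, none of them from the documents. They show that the problem could matter, not that it has this size.

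The documents do not support saying that the comparison is known to be biased, or that matching fails. They leave open how much selection the matching removes.

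**What to change.** In Objectives {7} and Statistical methods {20a}, replace the natural-experiment label with a matched observational cohort. State that current symptoms and motivation at entry are unrecorded for controls. Report the risk-matched difference as an association, and reword the passage on diminishing program benefit to agree.

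Add a placebo-date analysis as a partial falsification check, for outcomes that exist before enrolment (visits, admissions, prescriptions). Move every index date 12 months earlier, rematch using only records before that date, and compare the following 12 months. Rematching is essential, because a match that uses the placebo year would push its difference towards zero. Say beforehand that a clear difference shows residual selection, that a near-zero one does not rule out a peak confined to enrolment, and that the placebo difference will not be subtracted as a correction.

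The cost is one extra matching build within the planned extract, a look-back of only 12 months for the youngest children, no coverage of school-age outcomes, and a weaker causal claim.

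### A population cohort matched only on demographics is made a control for BEAM's effectiveness on administrative outcomes, although BEAM parents are selected mainly on current symptoms

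*Protocol article*

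**What the plan says.** **The aim and hypothesis.** Objectives {7} states: "We additionally aim to evaluate BEAM’s effectiveness in improving long-term health and psychosocial child and family outcomes relative to two population-based control cohorts". The hypothesis is improvement in administrative records of physical and mental health and in "developmental outcomes relative to the population-average and risk-matched cohorts". Neither cohort is labelled descriptive, and no rule says which one carries the inference or that both contrasts must succeed.

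**The two cohorts.** Statistical methods {20a} says that the population-average "control cohort will be comprised of parents who match the basic demographics of BEAM participants and their children", with age and number of children as examples. The risk-matched cohort consists of parents "who match the demographics, physical health, mental health, child developmental, and service utilization characteristics of BEAM participants and their children", built with a high-dimensional propensity score.

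**The contrast.** Trial design {8} speaks of changes relative to parents in the community. Statistical methods {20a} compares trajectories across BEAM, risk-matched and population-average families to describe stable, cumulative or delayed benefits for children.

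**Who enters BEAM.** Under Inclusion and exclusion criteria: "Parents must also self-report: moderate-to-severe symptoms of depression", or elevated anxiety, parenting stress or anger, at T0. Parents below every cut-off may still enter on clinical judgement of need. Crisis services are one of the four recruitment streams. There is no allocation.

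**The data window.** Records run from childbirth (as early as January 2018) to as much as five years post-intervention, ending June 2030. Children are 24–71 months old at enrolment.

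**The concern.** A comparator for effectiveness has to show what would have happened to the BEAM families without BEAM. A cohort alike only in age and family size cannot do that for parents who were enrolled because they were currently unwell.

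Two biases follow. In levels, BEAM families are expected to be worse both before and after, so the programme looks bad. In change, part of the elevation at enrolment is temporary and fades without treatment, while the unselected cohort has no such peak. The fading can then pass for benefit.

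The hypothesis names both cohorts and sets no rule between them. A favourable contrast with the population-average cohort could therefore be reported as support for effectiveness. The shape of the trajectories is affected too: Statistical methods {20a} reads benefits confined to the first year as a sign that further intervention may be required.

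**Working it through.** The document gives no sample size, effect or SD for the administrative comparison, so there is no figure to reproduce. N = 400 was set for the self-report primary outcome. Everything below assumes **zero programme effect**. Inputs marked (A) are assumptions.

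**Step 1: the general form.** Let a share p of parents exceed the cut-offs on a normal screening score. Their mean elevation is λ = φ(c)/p, where c is the cut-off on the standard normal scale. For p = 0.20 (A), λ = 1.40; for p = 0.30 (A), λ = 1.16. If an outcome correlates ρ0 with the screening score before enrolment and ρ1 after it:

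- level difference after enrolment = ρ1 × λ (BEAM worse);
- difference in change = (ρ1 − ρ0) × λ (negative means apparent improvement).

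With p = 0.20 and ρ1 between 0.15 and 0.40 (A), BEAM is worse in level by 0.15 × 1.40 = 0.21 SD to 0.40 × 1.40 = 0.56 SD. The change bias is zero if ρ1 = ρ0, so its existence depends on how the windows are chosen.

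**Step 2: put in the windows.** Assume the underlying level has a stable share t = 0.4–0.6 (A) and a temporary share 1 − t that decays in both directions from T0 with time constant τ = 0.25–2 years (A). Screening reliability is 0.8 (A), and p = 0.20–0.30. The temporary part averaged from a to b years away from T0 is

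A(a, b) = τ/(b − a) × [exp(−a/τ) − exp(−b/τ)].

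Spurious improvement = √0.8 × λ × (1 − t) × [A(pre) − A(post)], in SD of the underlying level. Children aged 24–71 months give about 2 to 6 years of records from birth, but a shorter baseline could be chosen. The post-window starts at 0.25 year, after the 12-week programme.

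Worked case: p = 0.20, t = 0.5, τ = 1. The multiplier is 0.894 × 1.40 × 0.5 = 0.626. With five years of follow-up, A(post) = A(0.25, 5.25) = 0.155.

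| Pre-window | A(pre) | Worked case | Range over all assumed values |
|---|---|---|---|
| 0.5 year | 0.787 | 0.626 × 0.632 = 0.40 | 0.17 to 0.48 |
| 1 year | 0.632 | 0.626 × 0.477 = 0.30 | 0.09 to 0.36 |
| 2 years | 0.432 | 0.626 × 0.277 = 0.17 | 0.04 to 0.23 |
| 4 years | 0.245 | 0.626 × 0.090 = 0.06 | 0.02 to 0.08 |
| 6 years | 0.166 | 0.626 × 0.011 = 0.01 | −0.01 to 0.02 |

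With only one year of follow-up, A(0.25, 1.25) = 0.492. A 4-year pre-window then gives 0.626 × (0.245 − 0.492) = −0.15 SD, so the sign reverses. An outcome that correlates r with the underlying level shifts r times as much: at r = 0.3 (A) the one-year figure falls from 0.30 to 0.09 SD.

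**Step 3: what a given bias does to a test.** More than 80% opt in to linkage, so take about 320 of 400 families, with one control each (A) and outcome autocorrelation 0.5 (A). The SD of change is √[2 × (1 − 0.5)] = 1, and the SE of the difference is √(2/320) = 0.079. In simulation, a bias of 0.07, 0.21 or 0.35 SD gives a false favourable result in 15%, 75% or 99% of trials, against a nominal 2.5%. With no bias the rate is 2.5%.

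**Step 4: the risk-matched cohort.** Under the same model, matching on the pre-enrolment outcome leaves a difference of λ × (ρ1 − 0.5 × ρ0). For ρ0 = 0.5, ρ1 = 0.25 this is 0. For ρ0 = 0.5, ρ1 = 0.40 it is 1.40 × 0.15 = 0.21 SD against BEAM. In the simulated cases the false favourable rate was 0–3%. This contrast is much safer but not free of selection on current symptoms.

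**The case against.** The strongest reply is that the safeguard is already in the sentence. The hypothesis names both cohorts, and the methods compare all three trajectories. The drift of the risk-matched families against the population would itself show much of the change to expect without BEAM. This has force, and if success required both contrasts, the risk-matched one would guard the conclusion. But no such rule is stated. An analysis plan that is not shown might supply one; the fault here lies in a stated hypothesis, not in an omitted detail.

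The second reply concerns size. Records reach back to childbirth, and a long pre-window can remove the change bias altogether. Children were not themselves screened on symptoms, so literacy or vaccination need not drift because a parent screened high. Entry is through any of four scales or by judgement, so selection is not one sharp cut. All of this stands. A reader might infer that regression to the mean must favour BEAM, or might size it from the self-report scales at T0, T1 and T2. The documents support neither: those scores do not exist for the control families, and the article does not fix the windows.

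The third reply is that closing the gap to the provincial norm is a fair question for scaling. It is, and the comparison can stay as description.

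**Conclusion.** The concern holds for the role given to the population-average cohort. Its lack of exchangeability with BEAM families does not depend on any window: one group is selected mainly on current symptoms or need and the other is not. A level comparison is biased against BEAM. A change comparison can be biased, often in BEAM's favour.

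Size and direction are not fixed by the document. Under the assumed values, with five years of follow-up and an outcome that tracks symptoms fully, the spurious improvement runs from about zero (6-year pre-window) to about 0.1–0.5 SD (a year or less). It is smaller for outcomes loosely tied to parental symptoms, and its sign can reverse when follow-up is short and the pre-window long. The test error rates in step 3 apply only if a bias of that size is present.

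A reader might also infer that the whole administrative comparison is invalid. The documents do not support that: the risk-matched contrast greatly reduces the problem. The point concerns a secondary aim and leaves the primary outcome and N = 400 untouched.

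**What to change.** In Objectives {7} and Statistical methods {20a}:

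1. Name the risk-matched cohort as the sole comparator for the administrative effectiveness hypothesis.
2. Keep the population-average comparison, with intervals, as a descriptive benchmark of distance from the provincial norm, and say that it is not read as evidence of programme effect.
3. State that risk matching uses administrative records, not T0 symptom scores, so some selection on current symptoms may remain.

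The cost is wording only, with no new data. The downside is that one fewer comparison can be presented as evidence of benefit.
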